
### Measurement of outcomes at follow-up

Participants are asked to complete the follow-up questionnaires independent of their parent(s). Adolescents who do not complete the follow-up questionnaires are contacted by mail, email, or text (depending on their preference) every 2 weeks for a total of 3 times, and then telephoned once, to be reminded. A CAD$50 gift certificate is provided to participants at each of the 1-, 6-, 12-, and 18-month time points to acknowledge their time and commitment to questionnaire completion. Documentation of first ACHD visit is sought during a medical record review 18 months after enrollment. If the first ACHD appointment has not happened at that time, documentation of the first ACHD appointment will be reassessed at study closeout.

### Proposed sample size

The sample size is based on the primary outcome, change in the TRAQ score. In our team’s CHAPTER 2 study,^7^ the mean difference from baseline of the TRAQ self-management score was 0.71 ± 0.90 at 18 months in the control group and 1.12 ± 0.86 in the intervention group (effect size 1.12 − 0.71 = 0.41). For the current study, the noninferiority margin between the intervention and control groups at 18 months has been conservatively set at 0.40. This represents less than half of a standard deviation. Anticipating the mean difference from baseline of the TRAQ self-management score of 1.12 ± 0.86 in the control (nurse-only) group (consistent with our CHAPTER 2 data) and estimating that a mean difference from the baseline in the App group will be no more than 0.40 less at 18 months (ie, 1.12 − 0.40 = 0.72), with 1-sided α = 0.025, standard deviation 0.8, and 80% power, we would require 64 patients per group (total 128). To account for clustering due to randomization by weeks with estimated average number of patients per cluster (per week) to be 2 and intraclass correlation coefficient = 0.1, the design effect is equal to 1.1, which increases the sample size to 71 per group (142 total). The CHAPTER 2 study had a dropout rate of 26% by 18 months.^7^ Assuming a 30% dropout rate, we aim to enroll 102 participants per group (204 total).

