### Group allocation

Participants are randomized by clusters defined by week of attendance in the pediatric cardiology clinic. As “week,” not study participant, is the unit of randomization, this is a cluster randomization design. This method of randomization (1) prevents 2 adolescents in the same waiting room being allocated to different groups and (2) facilitates scheduling of study RNs who are available at short notice to meet with participants. Cardiologists are not informed of group assignment, preventing potential bias by cardiologist cointervention. There is a 1:1 allocation of intervention:control weeks, stratified by site, using permuted blocks of randomly varying sizes of 2 and 4. We anticipate enrollment of 0-2 patients per week, that is, cluster size will be ≤2. To determine which weeks are intervention weeks vs control weeks, a biostatistician prepared a randomization sequence that is unique for each site. Allocation tables were locked and sent under password protection directly to a coordinator at each site.

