### Primary outcome

The primary outcome is the change in the Transition Readiness Assessment Questionnaire version 5.0 (TRAQ) score, between baseline and 18 months. The TRAQ is the most rigorous transition readiness scale for adolescents.^16^ This 20-item scale has 5 subscales (Appointment Keeping, Tracking Health Issues, Managing Medications, Talking with Providers, and Managing Daily Activities). The overall scale has high reliability (Cronbach’s α 0.94). Item and mean scores range from 1 (low) to 5 (optimal).^17^ The TRAQ has a grade 5.7 reading level and takes approximately 5 minutes to complete. We have not observed a ceiling effect; the mean self-management score at baseline in the CHAPTER 2 study (16- to 17-year-olds) was 2.9 ± 0.8.^7^ All baseline questionnaires are completed in the cardiology clinic before meeting with a study RN.

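### The sample size uses a standard deviation of 0.8 where the same sentence anticipates 0.86, so the stated 80% power does not follow from the plan's own inputs

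*Protocol article*

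**What the plan says.** All the sizing inputs stand in one paragraph of the Protocol article, under Proposed sample size.

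- For the earlier CHAPTER 2 study it reports 18-month changes of "0.71 ± 0.90 at 18 months in the control group and 1.12 ± 0.86 in the intervention group".
- The noninferiority margin is 0.40, of which the article says: "This represents less than half of a standard deviation".
- For this trial it continues: "Anticipating the mean difference from baseline of the TRAQ self-management score of 1.12 ± 0.86 in the control (nurse-only) group".
- The same sentence ends with the calculation itself: "with 1-sided α = 0.025, standard deviation 0.8, and 80% power, we would require 64 patients per group (total 128").
- A design effect of 1.1 (two patients per week, intraclass correlation 0.1) raises 64 to 71 per group, and 30% dropout raises that to 102 per group, 204 in total.

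Three other sections matter. Primary outcome defines the outcome as a change from baseline to 18 months and gives the CHAPTER 2 baseline self-management score as 2.9 with SD 0.8. Group allocation says: "We anticipate enrollment of 0-2 patients per week, that is, cluster size will be ≤2". Quantitative data analysis plans linear mixed models in which every outcome score is adjusted for its baseline value.

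**The concern.** The primary outcome is a change score, and the only change SDs in the article are 0.86 and 0.90. The calculation uses neither. It uses "standard deviation 0.8", without explanation, in the sentence that has just anticipated 0.86. Rounding does not account for this, because 0.86 to one decimal is 0.9. The value 0.8 does match the baseline SD under Primary outcome, but that describes the spread of scores at one visit, not of changes between two visits. Whether it is the source of the figure is not stated.

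What is at stake is the stated power. In a noninferiority trial, less power means a wider confidence interval and a greater chance that an App that is truly as good as nurse teaching fails to be shown noninferior. A reader who takes the 80% at face value cannot tell whether it describes a raw comparison of change, which the anticipated SD does not support, or an adjusted analysis that the paragraph never mentions.

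**Working it through.** **Inputs** (all from Proposed sample size unless noted)

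- margin M = 0.40
- one-sided α = 0.025, 1:1 allocation
- SD used 0.8; SD anticipated for the nurse-only group 0.86; CHAPTER 2 control arm 0.90
- design effect 1 + (2 − 1) × 0.1 = 1.1
- dropout 30%
- baseline SD 0.8 (Primary outcome)
- true difference 0. The article does not state this; it is the value that reproduces n = 64.

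**Formula.** With n per group, the standard error is SE = SD × √(2/n). Power is the probability that a noncentral t variable with 2n − 2 degrees of freedom and noncentrality M/SE exceeds the 97.5% point of the central t distribution. The normal approximation gives results within about one percentage point.

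**Step 1: reproduce the plan (SD 0.8).**

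- At n = 64, SE = 0.8 × √(2/64) = 0.1414, the noncentrality is 0.40/0.1414 = 2.83, and power is 80.1%. At n = 63 power is 79.5%, so 64 is the smallest adequate n.
- 64 × 1.1 = 70.4, rounded up to 71.
- 71/0.70 = 101.4, rounded up to 102 per group, 204 in total.

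The arithmetic is right. Only the input is in question.

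**Step 2: same numbers, anticipated SD.**

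| SD | n per group (effective) | SE | M/SE | Power (t) |
|---|---|---|---|---|
| 0.80 | 64 | 0.1414 | 2.83 | 80.1% |
| 0.86 | 64 | 0.1520 | 2.63 | 74.2% |
| 0.86 | 71/1.1 = 64.5 | 0.1514 | 2.64 | 74.6% |
| 0.90 | 64 | 0.1591 | 2.51 | 70.4% |

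The normal approximation at SD 0.86 gives 74.9% and 75.2% for the second and third rows. The 0.90 row is context only: it comes from the CHAPTER 2 control arm, which neither arm of this trial repeats.

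**Step 3: n for 80% power at SD 0.86, unadjusted.** 74 per group (power 80.2%; 73 gives 79.7%). Then 74 × 1.1 = 81.4, rounded up to 82, and 82/0.70 = 117.1, rounded up to 118 per group. That is 236 enrolled, against 204.

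**Step 4: what baseline adjustment could do.** Let s0 = 0.80 be the baseline SD, s1 the 18-month SD and sd = 0.86 the change SD. The baseline-to-18-month correlation is

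r = (s0² + s1² − sd²)/(2 × s0 × s1),

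and the residual SD after adjustment is s1 × √(1 − r²). The article does not give s1, so it is varied as an assumption:

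| Assumed s1 | r | Residual SD | Power at 64 per group |
|---|---|---|---|
| 0.80 | (0.64 + 0.64 − 0.7396)/1.28 = 0.42 | 0.73 | 87% |
| 0.90 | (0.64 + 0.81 − 0.7396)/1.44 = 0.49 | 0.78 | 82% |
| 1.00 | (0.64 + 1.00 − 0.7396)/1.60 = 0.56 | 0.83 | 78% |

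To bring 0.86 down to 0.80, adjustment must remove 1 − (0.80/0.86)² = 13.5% of the variance of the change. That happens for s1 up to about 0.93.

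**Step 5: the margin in SD units.** 0.40/0.86 = 0.47, 0.40/0.90 = 0.44, and 0.40/0.80 = 0.50.

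**The case against.** The strongest reply is that the trial will not be analysed as a raw comparison of change. The planned models adjust for baseline, so the SD that governs precision is the residual SD, which should be no larger than 0.86 and could well be below 0.80. This stands. A reader might infer from the mismatch that the design delivers only about 74%. The document does not support that, because the figure belongs to the unadjusted comparison alone. But the reply does not rescue the stated 80% either. The sample-size paragraph does not mention adjustment, gives no correlation, and presents its inputs as raw change; at an 18-month SD of 1.0 the adjusted power would still be slightly below 80%.

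Four further criticisms are tempting and should not be made.

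- **The margin described as under half an SD.** It would be wrong against 0.8, where 0.40 is exactly half. But the remark follows directly on the change SDs 0.90 and 0.86, and against those it is true.
- **The design effect.** Group allocation caps clusters at two, so an average of two is the ceiling and 1.1 is a conservative upper bound. The article does not say how often clusters will be smaller.
- **The App change of 0.72.** A reader might take this as the expected result, which would make the power calculation meaningless. It is the noninferiority limit, and n = 64 is obtained at the conventional true difference of zero.
- **The score's name.** The inputs are labelled a self-management score, which is not one of the subscales listed under Primary outcome ("This 20-item scale has 5 subscales (Appointment Keeping, Tracking Health Issues, Managing Medications, Talking with Providers, and Managing Daily Activities"). The article may simply use the phrase for the TRAQ; whether CHAPTER 2 used a different score cannot be settled from this document.

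**Conclusion.** The point holds as an unexplained inconsistency in an input. The plan anticipates a change SD of 0.86 and calculates with 0.8. On the anticipated SD, the planned numbers give about 74–75% power for an unadjusted comparison of change, a shortfall of some five to six percentage points. This rests on a true difference of zero, the 1.1 design effect and 30% dropout.

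It is not a demonstrated loss of power under the planned analysis. With baseline adjustment, the same enrolment gives about 87%, 82% or 78% power for assumed 18-month SDs of 0.8, 0.9 or 1.0, taking baseline SD 0.80 and change SD 0.86. The 80% may therefore be attainable, but the article does not show it. The type I error, the margin and the enrolment target are unaffected.

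**What to change.** Keep the target of 204 and revise the sample-size paragraph.

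1. Reconcile 0.8 with 0.86: say where 0.8 comes from, or replace it.
2. Then do one of two things. Either restate power as about 74–75% on unadjusted change with SD 0.86; or base the stated power explicitly on the baseline-adjusted analysis, giving the assumed correlation and a range such as residual SDs of 0.73, 0.78 and 0.83 with power of about 87%, 82% and 78%.
3. State that the calculation assumes a true difference of zero between the arms.
4. Keep the remark that the margin is under half an SD, but tie it to SD 0.86 (0.47 SD).
5. Leave the design effect of 1.1 as it is.

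The cost is a few restated figures in one paragraph. No extra participants are needed.

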### Quantitative data analysis

Intention-to-treat analyses will be used, and all statistical tests will be 2-sided. Baseline characteristics of both groups will be summarized using descriptive statistics (eg, means, medians, standard deviations, frequencies, and proportions). Linear mixed models with random effects will be used to analyze the change in scores over time for each outcome variable. To account for the cluster randomization, randomization by 4 sites, and repeated individual values, effects of weeks (clusters), sites, and individual participant will be considered random. All outcome scores will be adjusted for the baseline in the models. To evaluate the effect of time on intervention, we will include an intervention group × time interaction in each model. Separate models will be developed for each outcome measure that include all data collection times of respective scores to assess treatment effects, with and without adjustment for baseline variables. Planned subgroup analyses are moderate vs complex CHD and by gender. Statistical analyses will be performed using SAS 9.4 (SAS Institute Inc, Cary, NC).

### Qualitative data analysis

Interviews will be transcribed verbatim, anonymized, and analyzed using reflective thematic analysis^25^ to identify and extract patterns in data about participants’ perceptions and views about the acceptability and usability of the App (intervention group), or acceptability and value of the nurse-only teaching (control group). Thematic analysis will be used inductively to investigate the barriers and facilitators to the uptake of the App by adolescents. Attention will be given to how gender and severity of CHD (moderate vs complex) influences participants' experiences including their engagement with and uptake of the App. Transcription and data analysis will occur concurrently to identify when new themes cease to emerge. To enhance the trustworthiness of the data analysis, 20% of the transcripts will be independently coded by [name], the lead qualitative researcher. To analyze the nursing logs and field notes for the control group, summative content analysis^26^ will be used to identify the frequency of the words employed and the potential meaning for each term to describe the participant’s interactions during the sessions with the nurse. Interviews, logs, and field notes will be analyzed independently by 2 team members and reviewed by the lead qualitative researcher. The qualitative research team will follow all steps to increase the validity, credibility, transferability, and dependability of findings by adhering to guidelines for publication of qualitative research studies.^27^

### Cost-effectiveness analysis

Total and incremental health care costs of providing app-based and nurse-only care will be determined. We anticipate that App-based care will have lower cost given the reduction in nursing time compared with standard nurse-only care, and if noninferior, determining total and incremental costs of providing App or nurse-only care will result in actionable results.

A microcosting approach will be used, comprising identification, measurement, and valuation of resources required for development and delivery of App-based or nurse-only care.^28^ This will include one-time costs (educational material and app development and design), intermittent costs (updated app and educational materials), and ongoing costs (IT costs, IT personnel, and health care professional time) and will be prospectively enumerated throughout the study. Valuation of resources will be based on current costs, for example, the wage rates of IT personnel and nurses. Annual per patient costs will be determined by estimating the scale and spread of one-time costs, frequency of intermittent costs, and capacity of health care providers (ie, how many patients can be provided transition care by one nurse), accounting for the size of participating programs. Sensitivity analysis will be conducted to account for scope and scale of programs (significant impact on one-time and intermittent costs) as well as a range of wage rates in various jurisdictions. We will use a similar approach to programmatic costing as our group has previously conducted.^29^

### Ethical considerations

The study has been approved by the Health Research Ethics Board at all participating sites. Written informed consent is obtained in all cases.

## Discussion

The READYorNot CHD study will rigorously evaluate a novel transition app compared with a previously established control^6^^,^^7^ (ie, nurse-only teaching) among older adolescents with moderate or complex CHD. The App content has been designed to meet the educational needs of adolescents with CHD.^30^ For example, given the high proportion of adolescents and young adults who experience gaps in care^31^, ^32^, ^33^ predisposing them to late cardiac complications,^34^ the App includes an emphasis that CHD is a lifelong condition that requires specialized care throughout adulthood. The App also addresses adolescent self-management skill development, including but not limited to medication management, appointment scheduling, development of a portable health summary (the SmartHeart Pass), and preparation for an elective hospital stay.

Li et al.^35^ recently published a systematic review of the usability and effectiveness of mobile health interventions, supporting transition in adolescents and young adults with chronic disease. Among 22 included studies, 18 (82%) involved a mobile app. Only 12 studies (55%) provided data on efficacy, and only 1 study was focused on the CHD population.^36^ The interventions ranged from simple text messages to complex interventions including games and engagement with health care providers. Six intervention themes were identified: medication monitoring and reminders, symptom tracking and monitoring, management goal setting, knowledge education and self-management skills training, incentives and reinforcement, and communication. Participants in these studies reported that apps were convenient, easy to use, and easy to access. However, some studies reported a decline in youth engagement with the app over time, as early as within 4 weeks.^36^^,^^37^ Adolescents and young adults preferred engaging elements such as visually appealing features, customization options, and entertainment functions, as well as disease-specific information, all of which were incorporated into the App. This review also reported that adolescents and young adults valued opportunities to communicate with their peers and health care providers. Although these features were not included, the App does include 1-way communication in the form of brief video messages of support from peers with affirming messages. This review demonstrated that overall, the evidence regarding the efficacy and long-term health benefits of these interventions is minimal, as most of the interventions were in the usability testing stage.

There is very limited literature with respect to transition app development in CHD. Lopez et al.^38^ previously developed an app for adolescents with CHD, with content that was informed by semistructured interviews of a large group of adolescents and young adults with CHD aged 15-22 years, parents, and 2 expert panels (3 adolescents per panel). Content includes a profile page with a diagram of the user’s native cardiac anatomy, a transition checklist, information on when to seek urgent medical care, the option for journal entries, and information about managing medications, answering doctors’ questions, and lifestyle topics including exercise, travel, and alcohol. Outcome data from this app have not yet been published. Han et al.^36^ conducted a randomized clinical trial of nurse-led transition teaching to evaluate if including a demonstration of 5 standard phone apps (Contacts, Calendar, Notes, Camera, and Reminders), currently available on iOS and Android phones, benefits adolescents’ self-management skills. The control group received the same teaching content, but without incorporating these apps. The purpose of encouraging youth to use these apps, collectively referred to as “Just TRAC it!” was to promote the development of their self-management skills.^36^ Transition readiness skills increased in both study groups, with no clear benefit for those in the “Just TRAC it!” group. However, most participants in the App group reported these 5 apps to be very or extremely useful, and by 6 months after enrollment, 100% of participants stated that they would recommend it to others.^36^

The development of the App was a resource-intensive process, requiring more than 12 months of content review by experts in CHD care and a Youth Advisory Council, despite the advantage of being able to develop the App on the platform of a pre-existing app for youth with BBD. However, if shown to be effective, the App has the potential to reduce dependence on nursing resources going forward, warranting a cost-effectiveness analysis. Nursing time and space in clinical settings can be barriers to delivering transition preparation for some programs. Furthermore, the App could reduce barriers imposed by social determinants of health. For example, living remotely from cardiac centers or having employment that does not enable time off can serve as barriers to attending cardiology appointments and reduce the likelihood of benefitting from nurse-only teaching. The App is also highly accessible; it will be continuously available to the intervention group participants for an 18-month period, allowing them to review the content repeatedly as needed. A racially and ethnically diverse study of adolescents and young adults with CHD reported that 94% had access to a mobile phone,^38^^,^^39^ and most individuals always keep their phone with them. In contrast, nurse-only teaching is a time-limited event, and although control group participants will have the opportunity to take home a portable health summary and diagram of their CHD, not all content will always be available to them.

### Potential limitations

Several threats to internal and external validity exist, which include the following: (1) cointervention: awareness of the study and of the need for health care transition may influence what cardiologists say to participants; however, both groups will benefit equally, and this will not create a bias toward one study group. Cardiologists will be unaware of group allocation, though they may inadvertently find out their patient’s group assignment. (2) Loss to follow-up: we anticipate that approximately 30% of participants will not complete questionnaires at all time points despite repeated reminders by text, email, or phone. A $25 gift card for completion of questionnaires at each time point was increased to $50 for participants in both study groups. When patients miss appointments, clinics will use all available contact information to arrange another appointment and keep patients in care. Participants who have not attended the ACHD clinic by the end of the study period will be censored and will still contribute to the secondary outcome of excess time to ACHD care. (3) App uptake: the App takes approximately 4 hours to get through, which is significantly more time-consuming than meeting with a nurse for an hour. Intervention group participants will be encouraged to do 2-3 modules per week, each taking 10-15 minutes. Videos, games, “trophies,” and other interactive features have been built into the App to keep users engaged. To encourage App completion, participants’ names are entered into a draw to win a pair of earbuds for each module they complete, which may bring into question real-world uptake of the App. Control-group participants are also entered into a draw for earbuds based on the number of questionnaires completed. (4) If there are delays in first adult clinic appointments resulting in excess time to ACHD care, reasons for such delays are unlikely to be well documented in the medical record and therefore unavailable to the study team. (5) The App group requires a brief teaching session with a nurse (Table 1), so access to the App is not independent of nurse teaching. However, App group nurses are different from “nurse-only” group nurses at all sites and receive separate training, to avoid contamination of the interventions.

In summary, the READYorNot CHD study is a multicenter, cluster randomized clinical trial comparing a novel transition app with limited nursing teaching to comprehensive nurse-only transition teaching for 16- to 17-year-olds with moderate or complex CHD. We are evaluating self-management skills, CHD knowledge, self-efficacy, time to first ACHD appointment, qualitative outcomes, and cost-effectiveness. The results of this study will inform patients, pediatric cardiology programs, and policy makers in judging whether this App provides clinically meaningful outcomes for adolescents and young adults living with CHD.

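### Only the control arm's earbud draw rewards returning outcome questionnaires, an avoidable difference between arms in how the primary outcome is collected

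*Protocol article*

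**What the plan says.** The two draws are described in the protocol article under Potential limitations, in the item on App uptake. For the App arm, "participants’ names are entered into a draw to win a pair of earbuds for each module they complete". For the control arm, "Control-group participants are also entered into a draw for earbuds based on the number of questionnaires completed". No entry for returning a questionnaire is described for App participants. The article discusses the draw only as something that may make App uptake look better than it would be in practice, and does not consider its effect on follow-up.

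The main questionnaire incentive is equal. Measurement of outcomes at follow-up states that "A CAD$50 gift certificate is provided to participants at each of the 1-, 6-, 12-, and 18-month time points", and Potential limitations confirms that "A $25 gift card for completion of questionnaires at each time point was increased to $50 for participants in both study groups". The reminder procedure is described once, without distinguishing the arms.

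On expected loss, "we anticipate that approximately 30% of participants will not complete questionnaires at all time points despite repeated reminders by text, email, or phone". Proposed sample size applies a single 30% rate to both groups. Primary outcome defines the endpoint as TRAQ change from baseline to 18 months, and Protecting against sources of bias states that participants know their allocation.

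**The concern.** TRAQ is self-reported, and a participant who does not return the 18-month questionnaire has no primary outcome. A reward for returning it that exists in one arm only is an arm-specific influence on who is observed.

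Timing may add to this. App participants are encouraged to finish all 20 modules within 3 months, so for those who do, the module draw has no further entries to offer when the 18-month questionnaire is due. A draw that counts questionnaires can still reward return at that point. The article does not say when the draws are held.

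The direction matters because this is a noninferiority trial. If the App arm loses more participants, and those lost are the less engaged and less ready, the App participants who remain look better than the arm as a whole. The comparison then leans toward declaring noninferiority.

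**Working it through.** **1. The plan's own figure.** Inputs from Proposed sample size: margin 0.40, SD 0.8, one-sided α 0.025, power 80%. A noncentral t calculation with no true difference gives power 0.795 at 63 per group and 0.801 at 64, so 64 reproduces. The design effect is 1 + (2 − 1) × 0.1 = 1.1, and 64 × 1.1 = 70.4, rounded up to 71. With 30% loss, 71 / 0.7 = 101.4, rounded up to 102 per group (204 total). The stated sample size is not in dispute.

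**2. Standard error.** SE = 0.8 × √(2/64) = 0.1414. With 102 per arm, 75% return in controls, 65% in the App arm and design effect 1.1, the effective numbers are 76.5/1.1 = 69.5 and 66.3/1.1 = 60.3. Then SE = 0.8 × √(1/69.5 + 1/60.3) ≈ 0.141, the same value.

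**3. Shift among completers.** Let δ be completers' mean change minus non-completers' mean change, equal in both arms, and let d be the proportion lost. The completer mean is the arm's true mean plus δ × d. The App-minus-control difference among completers is therefore shifted by δ × (d_App − d_control).

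**4. Error at the margin.** If the true difference is exactly −0.40, the chance of declaring noninferiority is Φ(shift/0.1414 − 1.96), which is 2.5% when the shift is zero.

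Neither δ nor the return gap is in the documents. Both are assumptions, shown as a range:

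| App-arm return lower by | δ | Shift | Share of 0.40 margin | One-sided error |
|---|---|---|---|---|
| 3 points | 0.3 | 0.03 × 0.3 = 0.009 | 2% | 2.9% |
| 3 points | 0.5 | 0.03 × 0.5 = 0.015 | 4% | 3.2% |
| 10 points | 0.3 | 0.10 × 0.3 = 0.030 | 8% | 4.0% |
| 10 points | 0.5 | 0.10 × 0.5 = 0.050 | 13% | 5.4% |

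**5. Sign.** The shift is the product of two unknown signs. If δ is negative (non-returners do better) or if controls return less, but not both, the shift runs against the App.

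**6. Power.** With 102 per arm, SD 0.8 and design effect 1.1, power is 0.813 at 30% loss in both arms and 0.811 at 25% in controls and 35% in the App arm. Even at 20% and 40% it is 0.805. Unequal loss around 30% hardly affects power; the issue is bias only.

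**The case against.** The strongest objection is that the draw is minor beside the common incentive. Both arms are offered 4 × CAD$50 = CAD$200 for the follow-up questionnaires and receive the same reminders. Extra chances at a pair of earbuds may move return very little, and at a 3-point gap the effect is close to negligible. This stands, and is why the range above starts there.

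The App arm's module draw and 18 months of App access might also keep participants in touch with the study and narrow or reverse any gap. This too is possible, and the documents cannot settle it.

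A reader might infer a return gap of 15 points, which with the same δ would give a shift of 0.045 to 0.075. Nothing in the article supports a particular gap; it gives only the 30% planning figure and a 26% historical dropout.

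A reader might also infer that the mixed model has only baseline and 18-month TRAQ to work with. The article defines the primary contrast between those two times but does not say that TRAQ is collected only then. Quantitative data analysis plans to use all collection times of each score and to adjust for baseline. The figures above are for completers and take no credit for this, so the planned analysis should be less affected. It would still not remove bias from missingness that depends on the unobserved 18-month score.

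Finally, the word for addition in the control-arm sentence could be read to mean that App participants earn questionnaire entries too. The more natural reading is that controls have a draw as well, with a different trigger. If the other reading is what happens at the sites, the imbalance disappears and only the wording needs correcting.

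**Conclusion.** The point holds as a cheap improvement. As written, only the control arm has a draw tied to returning the questionnaires that carry the unblinded, self-reported primary outcome, and nothing else in the article offsets that particular difference.

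The effect is probably small. A shift of about 0.01 to 0.05 toward noninferiority, with one-sided error of about 2.9% to 5.4%, rests on three assumptions: App-arm return 3 to 10 points lower, non-returners' change 0.3 to 0.5 lower, and the same deficit in both arms. These figures illustrate what such a gap would do and do not predict this trial's result. The documents do not support the stronger conclusion that the draw will produce differential loss or a false finding of noninferiority.

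**What to change.** For all remaining follow-ups, give both arms the same draw entry for each completed questionnaire, and keep the module draw as a separate incentive for App uptake. App participants would then have two draws against one for controls, but the reward for supplying outcome data would be equal, which is what matters for ascertainment.

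Compare 18-month return by arm, before and after the change, and take that comparison into account when interpreting the noninferiority result. The change cannot help questionnaires already due, so the comparison is needed to show whether an imbalance arose earlier.

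The cost is an ethics amendment at the four sites, a few extra draw entries, and an incentive that differs between earlier and later follow-ups. The sample size does not change.
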